#### Health economics analysis

##### Measurement of costs and outcomes

We will calculate the incremental cost per quality-adjusted life year (QALY) gained of Community Navigators plus routine care compared to routine care over 14 months from a health and social care cost perspective, using the EQ-5D-5L to calculate QALYs. Secondary analyses will include (i) using the ReQoL to calculate QALYs; (ii) including wider societal costs such as productivity and absenteeism and use of voluntary services.

We will calculate the cost of delivering the Community Navigator intervention, including training and supervision based on activity reported by the Community Navigators. Unit costs for staff costs and Community Navigator costs will be taken from the Personal Social Services Resource Unit (PSSRU) [42]. We will collect all participants’ mental health service use information from health records, including contacts with community mental health staff and any use of inpatient or crisis services. Other health and social care resource use including primary care will be collected from an adapted CSRI at completed with researcher support at baseline, 8 months and 14 months asking about the past 6 months. The feasibility trial [7] identified that our TRD client group also had a range of physical health needs, so we will ask about planned and unplanned acute hospital resource use. Participants will be asked to report use of social prescribing schemes, befriending, peer support groups and other social clubs, organisation and voluntary sector groups as part of a bespoke questionnaire at baseline and each follow-up time-point to collect detailed information on any additional activities that might have occurred as a result of the intervention, with equivalent information also collected for the arm receiving only routine care. Health and social care resource use will be costed using NHS reference costs [43] and PSSRU [42]. For wider societal costs, we will ask about current employment status and for employed participants’ time off work sick in the past 6 months, with additional absenteeism and presenteeism information collected using the Work Productivity Activity Impairment Questionnaire [44], incorporated into the CSRI. This will be costed using the human capital approach. Costs of voluntary services and accommodation will also be included in wider societal costs.

QALYS will be calculated using the EQ-5D-5L and appropriate UK tariff as the area under the curve adjusting for baseline [45]. EQ-5D-5L has been shown to be a valid and responsive measure for depression [46] although there is limited evidence for TRD. The use of the EQ-5D-5L is recommended in the National Institute for Health and Care Excellence [47] allowing for comparisons across disease areas. In the Community Navigators feasibility study [7] (noting very small patient numbers), patients in the intervention group had a 0.19 increase in utility compared to 0.05 in the control group, indicated that the EQ-5D-5L may be sensitive to a treatment effect. However, to address potential limitations with the EQ-5D-5L, we will also calculate QALYs using the ReQoL and its published tariff, a measure of mental health-related quality of life.

We will report the mean incremental cost per QALY gained of the Community Navigator programme plus routine care, compared to routine care, over 14 months for all analyses. The denominator and numerator of the incremental cost per QALY gained will be calculated using regression analysis, accounting for baseline, site as a fixed effect and Community Navigator as a random effect. Other potential coefficients for inclusion will be considered as part of a health economics analysis plan signed off before database close. 95% confidence intervals, cost-effectiveness planes and cost-effectiveness acceptability curves will be calculated based on bootstrapped results. Assuming missing at random, we will use multiple imputation using chained equations to account for missing data. We will consider any potential missing not at random effects and sensitivity analyses for any uncertainty. All costs and consequences beyond 12 months will be discounted at a rate of 3.5% in line with NICE guidance.

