#### Secondary outcomes

We will also report PHQ-9 total score data at 4-, 11- and 14-month follow-up points.We will create two further variables from PHQ-9 scores for analysis at 8 and 14 months follow-up points: (a) recovery from depression, where PHQ-9 score will be dichotomised for analysis, where ≥ 10 is the clinical cut off for depression [20]; and (b) Substantial improvement in depression: a dichotomous variable for whether or not a reduction in PHQ-9 score since baseline of at least 5 points has been achieved, based on the established threshold for reliable and clinically significant change [29].The UCLA Loneliness scale (ULS-8) [30] is an 8-item scale measuring loneliness which has good established psychometric properties and has been used previously in mental health populations (all assessment points).The Generalised Anxiety Disorders Scale (GAD-7) [31] is a seven-item self-report measure of anxiety (baseline, 8 months follow-up, 14 months follow-up).The Questionnaire on the Process of Recovery (QPR) [32] is a 15-item self-report measure of personal recovery (baseline, 8 months follow-up, 14 months follow-up).The Multiple Identities Scale (MIS) [33] is a four-item self-report scale measuring multiple social identities (baseline, 8 months follow-up, 14 months follow-up).The Brief Rosenberg self-esteem scale (B-RSES) [34] is a 5-item scale measuring self-esteem (baseline, 8 months follow-up, 14 months follow-up).The Discrimination and Stigma Scale (DISC-12 subscale) [35] is an interview-based scale which measures experiences of mental health-related discrimination in key areas of everyday life and social participation, including work, marriage, parenting, housing, leisure and religious activities. To measure self-stigma, we will be using the four-item self-stopping behaviours subscale from the Discrimination and Stigma Scale (baseline, 8 months follow-up, 14 months follow-up).Lubben Social Network Schedule (LSNS-6) [36] is one of the most widely used questionnaires to quantitatively assess social network size and we will use the six-item Lubben Social Network Schedule to measure social network size (baseline, 8 months follow-up, 14 months follow-up).The EQ-5D-5L [24] is a five-item self-report health outcome measure (baseline, 8 months follow-up, 14 months follow-up).The Recovering quality of life (ReQoL) [25] is a 10-item self-report measure of quality of life developed for use across all mental health populations (baseline, 8 months follow-up, 14 months follow-up).Client Service receipt Inventory (CSRI) [26] is a tool used to collect information on the range of services and supports participants may use (baseline, 8 months follow-up, 14 months follow-up).Daytime Activities Questionnaire (all assessment points).The Credibility and Expectancy questionnaire [37] is a six-item scale that measures treatment expectancy and credibility. We will use a single-item adapted version (Baseline).

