### Participant timeline {13}

Table 1 shows the schedule of assessments.

**Table 1 Tab1:** Schedule of assessments

	**Screening**	**Treatment phase**		**Follow-up**	**Final visit**
**Visit no:**	1	2	3	4	5
	Screening and baseline assessment	4-month follow-up	8-month end-of-treatment follow-up	11-month follow-up	14-month (6 months post-treatment) follow-up
**Window of flexibility for timing of visits:**	n/a	+ 2 months	+ 3 months	+ 2 months	+ 3 months
**Informed consent**	YES				
**Eligibility confirmation (CIS-R and DJG measures)**	YES				
**Intervention credibility measure**	YES				
**All outcome measures and service user information listed in s. 10.1**	YES		YES		YES
**Depression (PHQ-9) and Loneliness (ULS-8) measures only**	YES	YES		YES	
**Randomisation**	YES				
**Trial intervention/treatment**		YES	YES		
**Adverse events active monitoring**	YES	YES	YES		
**Adverse events review**	YES	YES	YES	YES	
**Withdrawal**	YES	YES	YES	YES	YES

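### Two 6-month CSRI recalls cover at most 12 of the 14 months over which cost per QALY is reported, so CSRI-collected use in months 0–2 is not captured

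*Protocol article*

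**What the plan says.** All of the following is in the Protocol article.

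- **Horizon.** Under Measurement of costs and outcomes, the incremental cost per QALY is for the programme plus routine care "compared to routine care over 14 months from a health and social care cost perspective". The same section repeats the horizon: "compared to routine care, over 14 months for all analyses".
- **Source of the affected costs.** "Other health and social care resource use including primary care will be collected from an adapted CSRI", which is "completed with researcher support at baseline, 8 months and 14 months asking about the past 6 months". The list under Secondary outcomes gives the CSRI the same three time-points and no others.
- **Acute hospital use.** "we will ask about planned and unplanned acute hospital resource use". That sentence states no recall period.
- **Sickness absence.** This is asked "for employed participants’ time off work sick in the past 6 months". It enters the wider societal costs, which are a secondary analysis.
- **Sources not tied to the CSRI.** Mental health service use comes from health records, and intervention cost from activity reported by the Navigators. Neither carries a 6-month limit. Social and voluntary-sector activity comes from a separate questionnaire at baseline and every follow-up, with no recall period stated.
- **Visit timing.** In Table 1 (Participant timeline {13}), the row "Window of flexibility for timing of visits" allows +3 months at both the 8-month and the 14-month visit.
- **Handling.** QALYs are an area under the curve, and missing data are to be multiply imputed. The article states no rule for scaling or extrapolating resource use.

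**The concern.** A 6-month look-back suits the 14-month visit, which falls six months after the previous form. It does not suit the 8-month visit, which falls eight months after randomisation. The baseline form does not help, because it looks back from before randomisation.

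For the items that depend on the CSRI, the cost numerator therefore covers a shorter period than the QALY denominator. The uncovered months lie at the start of the 6-month phase of individual Navigator sessions (Intervention description {11a}). Intervention cost in those months is counted in full from Navigator activity, while any accompanying rise or fall in primary or social care use is not. Equal use in both arms would cancel in the incremental cost; a difference between arms in those months would be lost.

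Multiple imputation does not deal with this. When visits are on time, months 0–2 are unasked for every participant in both arms, so there are no observed values for that period to impute from.

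**Working it through.** **Inputs.** Horizon 14 months; CSRI forms after baseline at 8 and 14 months; recall 6 months (all from Measurement of costs and outcomes). Visit windows +3 months at each (Table 1). Time is counted from randomisation, in line with Intervention description {11a}, which has the programme end within 8 months of randomisation.

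**Formula.** A form completed at month v covers the interval from v − 6 to v. Coverage is the part of months 0–14 that lies in at least one such interval.

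**Attempt to reproduce the 14 months, visits on time.**
- 8-month form: 8 − 6 = 2, so months 2–8.
- 14-month form: 14 − 6 = 8, so months 8–14.
- Total 6 + 6 = 12 months. The stated 14 is not reached.
- Gap: months 0–2, which is 2/14 = 14% of the horizon and 2/8 = 25% of the period to the 8-month visit.

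**With the permitted windows.**

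| Visits held at months | Recall intervals | Months of 0–14 covered | Early gap | Gap between forms | Counted twice |
|---|---|---|---|---|---|
| 8 and 14 | 2–8, 8–14 | 12 | 2 | 0 | 0 |
| 8 and 17 | 2–8, 11–17 | 9 | 2 | 3 | 0 |
| 9 and 15 | 3–9, 9–15 | 11 | 3 | 0 | 0 |
| 11 and 14 | 5–11, 8–14 | 9 | 5 | 0 | 3 |
| 11 and 17 | 5–11, 11–17 | 9 | 5 | 0 | 0 |

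Over all whole-month combinations in the windows, coverage runs from 9 to 12 months and never reaches 14. When the second visit is at month 17, its form also reports months 14–17, which lie outside the horizon.

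**Size under an assumption.** Suppose the between-arm difference in CSRI costs is a constant d per month. The true 14-month difference is 14d. On-time forms record 12d. The shortfall is (14d − 12d)/14d = 2/14 = 14%. Under the same assumption, simply adding the two forms gives 12d whatever the visit dates, because the recall is always 6 + 6 months. Late visits then change which months are represented; cutting at month 14 without rescaling would lower the total further.

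**After the fix, same assumption, visits on time.** First form: 6d × 8/6 = 8d. Second form: 6d × 6/6 = 6d. The sum is 14d, which matches the horizon.

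**The case against.** The strongest reply is that this is a matter for the health economics analysis plan. The article says such a plan will be signed off before database close and promises sensitivity analyses for uncertainty; scaling a 6-month recall to the actual interval is the kind of step an article leaves out. This stands in part. The plan is not shown and may contain the rule, so the lack of a rule in the article is not the point. The point is that the recall stated in the article does not fill the horizon stated in the article. Later analysis can estimate the uncovered months but cannot recover answers that were not sought.

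Three further points stand and limit the scope.

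- A reader might infer that months 0–2 are not costed at all. The article does not support that: mental health contacts, inpatient and crisis use come from records, and intervention cost comes from Navigator activity.
- Acute hospital use is affected only if it is asked with the same recall, which the article does not say. Outcomes {12} says that mental and physical health service use is collected from records and the CSRI together, so some physical health use may come from records. Sickness absence bears only on the secondary societal analysis.
- The visit patterns at months 11 and 14, or 8 and 17, are the edges of what is allowed. Nothing shows how often they will occur.

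The reply that no material effect on the result has been shown is also correct. The article gives no cost figures, so the CSRI share of incremental cost is unknown.

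**Conclusion.** The point holds for CSRI-collected costs: other health and social care including primary care; acute hospital use if asked with the same recall; and sickness absence in the secondary societal analysis. On-time visits capture 12 of the 14 months and leave months 0–2 out. Within the visit windows the early gap runs from 2 to 5 months, a second gap of up to 3 months can open, and up to 3 months can be counted twice.

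The 14% understatement applies only to the CSRI component of the between-arm cost difference. It rests on even accrual and on-time visits. If the arms differ mainly in the early months the error is larger; if mainly later, smaller. It is tempting to read 14% as the error in the ICER or in total incremental cost. The documents do not support that, and neither the size nor the direction of the effect on the ICER can be computed from them. The clinical primary outcome is not touched.

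**What to change.** In the health economics analysis plan, before database close:

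1. Scale CSRI-reported use to the actual intervals by visit date: randomisation to the 8-month visit for the first form, and that visit to the 14-month visit for the second. The factor is interval length divided by 6 months. On time these are 8/6 and 6/6; with visits at months 11 and 14 they are 11/6 and 3/6. The second factor of 3/6 already removes the 3-month overlap, which should not be deducted again.
2. Truncate at 14 months. With visits at months 8 and 17, the 9-month interval is scaled by 9/6 and then 6/9 of it is kept.
3. Apply the same rule to sickness absence, and to acute hospital use if it shares the recall.
4. Report the unscaled result as a sensitivity analysis.

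Where forms are still to be collected, recall may instead be anchored to randomisation at the 8-month visit and to the last assessment at the 14-month visit, with the recall period used recorded on the form.

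**Cost.** Scaling needs a short section in the analysis plan and a constant-rate assumption for the uncovered months. Anchored recall avoids that assumption but lengthens recall at the first follow-up form to 8 months on time and up to 11 months with a late visit. It would also mix recall periods within the trial: recruitment began in September 2022, so the first 8-month visits fell due around May 2023, before the current protocol version of July 2023. For forms already completed, scaling is the only option.

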### Interim analyses {21b}

Trial recruitment and intervention engagement will be monitored and continuation criteria reviewed during the internal pilot phase of the trial. No interim analyses are planned.

### Methods for additional analyses (e.g., subgroup analyses) {20b}

Several additional analyses are planned. These include (1) an analysis to adjust for any baseline imbalance caused either by chance or missing data; (2) an analysis that includes PHQ-9 data from all five time-points (including baseline) using a 3-level mixed model; (3) an analysis to explore the mediating effect of loneliness on depression across the five time-points (main results permitting); (4) an analysis to explore the effect of baseline expectations and credibility of the intervention on the outcome (main results permitting). There are no planned subgroup analyses.

### Methods in analysis to handle protocol non-adherence and any statistical methods to handle missing data {20c}

Adherence to intervention will be described, e.g., in terms of the mean (SD) number of sessions attended. In addition, a complier average causal effect (CACE) analysis may be performed to adjust for any non-adherence to the intervention, where adherence to the intervention is defined as attendance at three or more meetings with Navigators. A further analysis may investigate whether there is a dose response effect of the number of Navigator meetings.

Withdrawals from the study, loss to follow-up and other missing outcome data will be summarised separately by randomised group. Potential bias due to missing data will be investigated by comparing the baseline characteristics of participants with and without missing values. Depending on the quantity of missing values, predictors of missingness may be identified. We will then perform a sensitivity analysis that includes these predictors of missingness as covariates in the primary analysis model. Various multiple imputation strategies may also be performed, if deemed appropriate, assuming either “missing at random” (MAR) or “missing not at random” (MNAR).

### Plans to give access to the full protocol, participant-level data and statistical code {31c}

The full trial protocol is publicly available on the funders’ website: Randomised controlled trial of the Community Navigator programme to reduce loneliness and depression for adults with treatment-resistant depression in secondary mental health services—NIHR Funding and Awards.

All requests for the participant-level dataset and statistical code should be submitted to the corresponding author for consideration. Access to anonymised data may be granted following review, involving the trial statistician and Priment Clinical Trials Unit team.

## Oversight and monitoring

### Composition of the coordinating centre and trial steering committee {5d}

Day to day management of the trial is overseen by the Trial Management Group (TMG), which consists of all the study co-Investigators and the trial manager and is chaired by the Chief Investigator. The TMG meets monthly. Study researchers and a representative of the Lived Experience Advisory Panel also attend TMG meetings.

Advice and monitoring of study documents, databases and procedures is provided by a team from the Priment Clinical Trials Unit, who support the study and undertake oversight responsibilities for quality assurance, delegated by the sponsor.

The study Lived Experience Advisory Panel (LEAP) consists of nine people with personal experience of depression or anxiety and using mental health services, who bring expertise by experience. The LEAP meets regularly, and LEAP members contribute to developing study documents and recruitment materials, recruiting and training Community Navigators, training study researchers, analysing qualitative data and contributing to writing up and disseminating study findings in due course. The LEAP group is supported and coordinated by the study peer researcher and co-Investigators from the McPin Foundation, a not-for-profit organisation which promotes service user involvement in research. The LEAP has no formal oversight responsibilities for the trial but provides additional scrutiny of trial documents and processes from a lived experience perspective.

The Independent Trial Steering Committee (TSC) has six members, including a clinical academic with extensive trials experience, an academic loneliness expert, two lived experience members both of whom bring experience of mental health practitioner roles, and an academic statistician and a health economist. The TSC meets at least annually. Approved minutes from TSC meetings and TSC recommendations are reported to the sponsors and the funders.

### Composition of the data monitoring committee, its role and reporting structure {21a}

The Data Monitoring and Ethics Committee (DMEC) has four members: an academic with expertise in TRD research and substantial trials experience, a senior academic psychiatrist, a statistician and a lived experience researcher who has a senior academic role. The DMEC has a specific remit to scrutinise participant safety and protocol breaches and can ask to see data sets and unblind data reports if required for these tasks. The DMEC meets at least annually and reports to the Chair of the TSC.

### Adverse event reporting and harms {22}

Serious adverse events (SAEs) are defined as any event which results in death, is life-threatening, requires hospitalisation or prolongation of existing hospitalisation, or results in persistent or significant disability or incapacity. SAEs will be monitored by researchers through a structured safety monitoring form completed at each follow-up assessment, and through feedback from Community Navigators, participants or involved clinicians at trial sites. Each SAE will be recorded on a case record form. The site Principal Investigator will liaise with the relevant clinical team and the participant if required to assess the event’s seriousness, expectedness and study-relatedness. SAE reports will be sent to the Clinical Trials Unit (delegated by the sponsor) and the DMEC Chair and clinical academic for review. Any serious, unexpected, study-related adverse events (SUSARs) will also be reported to the ethics committee within 7 days of the Chief Investigator becoming aware of them.

Any study-related harms which do not constitute SAEs will also be recorded using CRFs. The study team will also keep a log of any negative feedback or events relating to participants’ involvement in the study, to inform any needs for changes to trial processes or researcher training. These non-serious events will also be reported to the DMEC meetings for external review.

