### Outcomes {12}

All participants in the trial will be asked to complete self-report questionnaires at baseline, 8-month (end-of-treatment), and 14-month (6 months after end-of-treatment) follow-ups, and additional depression and loneliness ratings through phone or video calls at 4 and 11 months.

The primary outcome is depression symptom severity total score at 8 months end-of-treatment follow-up: measured by the Patient Health Questionnaire—PHQ-9 [20]. Secondary outcomes include measures of loneliness, depression, anxiety, personal recovery, multiple social identities, self-efficacy, self-sigma and social network size. For economic analyses, we will assess preference-based health-related quality of life using EuroQol EQ-5D 5 level (EQ-5D-5L) [24] and preference-based mental health-related quality of life using the Recovering Quality of Life (ReQoL) [25]. We will collect information about participants’ accommodation, employment status and use of mental and physical health services, using health records and an adapted CSRI measure [26]. The battery of measures for this trial was reviewed and refined following feedback from the feasibility trial and discussions with the Trial’s working group.

Participants will be asked to complete the following validated measures:

Screening measures collected at baseline:The Clinical Interview Schedule-Revised (CIS-R) [27] is a fully structured diagnostic instrument that was designed to be delivered by trained interviewers to assess minor psychiatric morbidity and generates diagnoses meeting ICD-10 criteria for depressive episodes.The DeJong Gierveld six-item Loneliness Scale (DJG-6) [28] is a 6-item, self-report measure of loneliness, yielding a total score and subscale scores for social and emotional lonelinessPrevious anti-depressant use

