### Sample size {14}

We will recruit 306 participants. The standard calculation to detect a 0.4 standard deviation (sd) difference in PHQ-9 depression score between arms with 90% power and 5% alpha requires 132 participants per arm. Adjusting for baseline PHQ reduces the sample size by *r*-squared, where *r* is the correlation between baseline and follow-up outcome values [38]. Assuming a correlation of 0.5 and 15% attrition (informed by the feasibility trial [7]) results in a sample size of 117 participants per arm. Assuming four sites, three navigators per site, and an ICC for clustering by navigator of 0.05, results in a design effect of 1.6 (based on 13 participants per navigator). Inflating the sample size for clustering in the intervention arm only (to 188), then adjusting group sizes to be equal, produces a sample size of 153 participants per arm.

In response to peer review comments, we have checked the sample size calculation using simulation and have found that we do obtain 90% power, as calculated, when analysing the data using a mixed model with ML, treating each control subject as a cluster of size 1. However, as noted by the reviewer, the confidence interval coverage and type I error are slightly improved by analysing the data using REML with the Kenward-Rogers adjustment. This results in a slight loss of power but is the analysis we now intend to use. The power to detect a (standardised) difference of 0.4 is reduced to 87%, or equivalently, we have 90% power to detect a difference of 0.42. This still provides 90% power to detect a minimum personally meaningful difference on PHQ-9 between groups of about 2 points [39].

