## Data collection and management

### Plans for assessment and collection of outcomes {18a}

Eligibility screening, baseline and follow-up data collection at 8-month end-of-treatment and 14-month follow-ups may be conducted through in-person meetings, video calls or phone calls, as the participant prefers. Four-month and 11-month data will be collected through a self-report online form or phone or video call only. The trial administrator or trial manager will check screening forms to confirm eligibility criteria are met before initiating randomisation through the trial electronic randomisation database. Checks of data completeness and accuracy will be made periodically by the Trial Manager or administrator, supported by the Clinical Trials Unit.

All study researchers will be trained in Good Clinical Practice (GCP) and will receive bespoke training from the Trial Manager and senior study researchers in conducting participant recruitment, including assessing capacity to consent, and study data collection measures. This will involve role play practice using measures with members of the study Lived Experience Advisory Group.

Data collection Case Record Forms are available from the corresponding author on reasonable request.

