### Plans to promote participant retention and complete follow-up {18b}

Participants’ decisions to withdraw from (a) the study intervention and (b) the trial will be recorded separately. Where a participant decides to disengage from seeing the Community Navigator before the scheduled end of the programme, the study research team will seek permission to continue to contact the participant to collect outcomes data at follow-up points. If a participant asks to withdraw from the research study, the research team will clarify whether the person (a) just wants no more contact from the researchers, or (b) wishes to withdraw their participation completely, including deleting any data previously collected. If the participant just wants no further contact with the researchers, the study team will retain data collected up to that point and collect data from patient records in accordance with the person’s consent.

Overdue follow-ups will be tracked using the study database. In the case of overdue follow-up visits, reasonable attempts will be made to contact the participant. These will include trying all contact routes provided by the participant and contacting the referring clinician.

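### The stated SAE sources are all reports from people; the psychiatric inpatient and crisis use already taken from records for everyone is not named as a safety source

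*Protocol article*

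**What the plan says.** **SAE sources.** The section on adverse event reporting and harms {22} names two routes. The first is active: "SAEs will be monitored by researchers through a structured safety monitoring form completed at each follow-up assessment". The second is feedback: "and through feedback from Community Navigators, participants or involved clinicians at trial sites". Its SAE definition includes any event that "requires hospitalisation or prolongation of existing hospitalisation". Health records are not mentioned as a source.

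**Record data.** The health economics section, under measurement of costs and outcomes, states: "We will collect all participants’ mental health service use information from health records". It says that this includes inpatient and crisis service use. Acute hospital use for physical health is handled differently: participants are asked about it. The retention section {18b} keeps record access open when someone wants no further contact with researchers: "the study team will retain data collected up to that point and collect data from patient records in accordance with the person’s consent".

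**Contacts at 4 and 11 months.** The data collection section {18a} says "Four-month and 11-month data will be collected through a self-report online form or phone or video call only", and the trial design section {8} also allows an online form. The outcomes section {12} describes the same contacts as "additional depression and loneliness ratings through phone or video calls at 4 and 11 months", with no online option.

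**Attrition.** The sample size section {14} has: "Assuming a correlation of 0.5 and 15% attrition (informed by the feasibility trial".

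**The concern.** A psychiatric admission meets the plan's SAE definition and is also a plausible reason for missing a research visit. Events may therefore be more frequent among people for whom the safety form is not completed. The trial will hold information on those admissions, because mental health service use is taken from records for everyone, but nothing in the safety section brings that information to the SAE log. Two tables in the final report, SAEs by arm and inpatient use by arm, could then disagree on the number of psychiatric admissions, and the DMEC would have reviewed the smaller set.

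The conflict over contact mode adds to this. If a 4- or 11-month contact can be a self-completed online form, the article does not say how a safety form monitored by researchers is completed on that occasion.

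**Working it through.** **1. Reproduce the figure that carries the 15%.**

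- Two-sided 5% alpha, 90% power, 0.4 SD: 132 per arm.
- Baseline adjustment with r = 0.5: 132 × (1 − 0.25) = 99.
- Attrition: 99 / 0.85 = 116.5, rounded up to 117.
- Design effect: 1 + (13 − 1) × 0.05 = 1.6, so 117 × 1.6 = 187.2, rounded up to 188 in the intervention arm.
- Equal arms: (117 + 188) / 2 = 152.5, rounded up to 153 per arm, 306 in total.

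This matches the protocol. The 15% is an allowance for missing outcome data and is applied correctly.

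**2. Number without the form at a missed visit.** 0.15 × 306 = 45.9, about 46 participants (about 23 per arm). The other 260 or so are seen.

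**3. Share of participants with an SAE who are missed.** Let L = 0.15 be the proportion lost, k the SAE risk in those lost relative to those seen, and c the proportion of SAEs in those lost that reach the log through clinician or Navigator feedback. Assume that all SAEs in those seen are found. Then

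share missed = L × k × (1 − c) / (1 − L + L × k).

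The document gives neither k nor c, so both are assumptions:

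| | c = 0 | c = 0.5 | c = 0.8 |
|---|---|---|---|
| Equal risk, k = 1: 0.15 × (1 − c) / 1.00 | 15% | 7.5% | 3% |
| Doubled risk, k = 2: 0.30 × (1 − c) / 1.15 | 26% | 13% | 5% |

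The share does not depend on the underlying SAE risk, but the counts do. If 10% of those seen have an SAE (assumed), equal risk gives 30.6 participants with an SAE in total, of whom 4.6, 2.3 or 0.9 are missed at c = 0, 0.5 or 0.8. Doubled risk gives 26.0 + 9.2 = 35.2, of whom 9.2, 4.6 or 1.8 are missed. Assumed risks of 5% or 20% halve or double these counts.

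**4. Set the sections side by side.**

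| Source | Whom it covers | Named for SAEs? |
|---|---|---|
| Safety form | Those assessed at that follow-up | Yes |
| Participant feedback | Those in touch with the trial | Yes |
| Navigator feedback | Intervention arm | Yes |
| Clinician feedback | Those with an involved clinician | Yes |
| Mental health records (inpatient and crisis use) | All participants; after contact stops, subject to consent | No |
| Participant report of acute hospital use | Those assessed | No, costing only |

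Of the sources in the article, the mental health records are the only one described as covering every participant, and the safety section does not use them.

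**The case against.** Several stronger readings are tempting, and the document does not support them.

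- *A reader might infer that attrition and online follow-up remove SAE detection.* They do not. Clinician and Navigator feedback does not depend on research follow-up. People expected to leave the mental health team within the 8-month intervention period are excluded, so a clinical team should normally be involved. The retention section also has researchers approach the referring clinician when a follow-up is overdue. What a missed visit costs is the systematic enquiry at that visit. The contact with the clinician is described there as a way to reach the participant, however, and not as a safety enquiry.
- *A reader might infer that someone who chooses the online form has no safety enquiry until the 8-month visit, whose window extends to month 11.* Table 1 schedules both adverse event monitoring and review at 4 months, and the safety section requires the form at each follow-up assessment. Nothing says that online completers skip it. The article leaves open how the form is completed online; it does not state a gap.
- *A reader might take one quarter of SAEs as the expected loss.* The 26% needs both doubled risk in those lost and no capture by feedback. The 15% is itself a planning assumption about outcomes. It does not show that 46 people are beyond their clinicians' reach, and a person who misses one visit may be seen at another.

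Two further objections have weight. First, this is a condensed article: the full protocol and the detailed monitoring plans are not shown, and they may contain a cross-check. That limits confidence. Still, the article states its SAE sources, and data that it says elsewhere will be collected for everyone are not among them. Second, the records cover mental health service use only, so they would not reveal physical hospital admissions. Study researchers are also blinded, and notes may mention a Navigator. Both limit what the remedy can do and who can carry it out; neither removes the reason for it.

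**Conclusion.** The concern holds in a limited form. As written, every named SAE source is a report from a person, and a record source already planned for all participants is left out although it bears directly on one SAE criterion. About 46 of 306 participants, at the planning assumption, would lose the systematic enquiry at a missed visit. The share of participants with an SAE who would be missed is unknown; 3% to 26% is the range over assumed relative risks of 1 to 2 and feedback capture of 80% to none, and feedback capture is the main driver. The calculation covers SAEs of any kind, and only the psychiatric and crisis admissions among them could be recovered from these records.

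This concerns the completeness of safety data. It does not affect the primary analysis or the sample size. The disagreement over the mode of the 4- and 11-month contacts is real, but it is an inconsistency in wording and does not show that safety enquiries are omitted.

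**What to change.** 1. In the adverse event section {22}, name the planned extraction of mental health inpatient and crisis use as an additional SAE source. Apply it identically in both arms, which matters because Navigator feedback arises only in the intervention arm. Include participants lost to follow-up, and those withdrawn from contact where their consent allows.
2. Have unblinded staff reconcile the extracted admissions with the SAE log before each DMEC report and before database lock. The trial manager and administrator are already unblinded.
3. State that these records do not cover acute physical hospital admissions, for which the trial relies on asking participants.
4. Reconcile the trial design {8}, outcomes {12} and data collection {18a} sections on the mode of the 4- and 11-month contacts. Include the safety questions in the online form, so that the requirement for a form at each follow-up assessment can be met when no researcher is present.

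The cost is protocol wording, a few added items in the online form and a reconciliation listing. The record data are already to be collected. The main downside is timing and staffing: some extraction has to be done before DMEC meetings, by unblinded staff.
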